### 1.5. Summary of rationale and knowledge gap.

Considering the current scenario described previously, where:

- There is an important disease burden caused by the growing epidemic of CVD.
- That from the point of view of the nation of Chile, it is necessary improve cardiovascular health in order to mitigate the epidemic.
- That from point of view of patients suffering a cardiovascular event, they need to prevent recurrent events, complications, death, and enhance their quality of life.
- Cardiovascular secondary prevention indicators have been poorly achieved.
- There are established interventions that can improve outcomes. Specifically cardiac rehabilitation is a strategy to organize secondary prevention, promoting medication adherence and healthy lifestyles through core components, with the exercise as the fundamental intervention.
- The standard model of exercise-based cardiac rehabilitation has been proven as an effective intervention to prevent cardiovascular death and hospitalizations, but most of this evidence stems from other regions than Latin America, and high-incomes countries in particular (14).
- The exercise-based cardiac rehabilitation programs are under-utilized and one of the barriers to deliver the service is cost involved and capacity (15).
- There are several alternative models of cardiac rehabilitation which may mitigate these barriers, which have been evaluated, but there remains gaps in evidence supporting some (24).
- That from point of view of the health systems, and in a resource-constrained era, we need to increase coverage to patients while at the same time that not increasing expenditures, such that the system is more efficient with greater impact at the population-level (22).
- A Low-Resource Setting Model of cardiac rehabilitation has been designed by an international council. This model recommends delivery of all core components adapted according to the available resources, in alternative settings and by lower-cost personnel (28).
- In spite of the Low-Resource Setting Model has been designed following a rigorous methodology in order to establish recommendations of the minimums, the fact that consider less supervised exercise sessions, less equipment, less monitoring, less education sessions, and less professional availability, could be make it less effective than standard model which has been evaluated against usual care. It needs to be tested in a real-world setting.

Is necessary to evaluate the effectiveness of a model of exercise-based cardiac rehabilitation more accessible, cheaper, more efficient, and designed for our local settings.

As the current knowledge is that the Standard Model of exercise-based cardiac rehabilitation is effective in reduce cardiovascular mortality and hospitalizations, compare the new model against usual care is not ethically possible, and to conduct a non-inferiority clinical trial seems to be the best alternative to generate local evidence, with better quality and minimal bias.

We anticipate that if non-inferiority of a lower-resource model is demonstrated, a more suitable and affordable model of cardiac rehabilitation will be available for patient and the health system in order to increase coverage, save resources, and improve cardiovascular health outcomes.

[figure not shown]

57

58

**2. Hypothesis:** A hybrid exercise-based cardiac rehabilitation model, which include 10 face-to-face sessions plus distance monitoring through text messages and phone calls is not inferior in effectiveness to the standard model. In other words, a program with less supervised sessions, using fewer human resources, and less equipment, but complemented with information and communication technology will not result in more recurrent cardiovascular events (is not inferior) than the standard model of cardiac rehabilitation.

### 3. Research goals:

**3.1 General goal:** To evaluate if a hybrid exercise-based cardiac rehabilitation program is not inferior to the standard exercise-based cardiac rehabilitation program.

### 3.2. Specific goals:

#### 3.2.1. Primary goal:

To evaluate if the prevention of recurrent cardiovascular events is not inferior in the hybrid exercise-based cardiac rehabilitation programs in comparison to the standard program.

#### 3.2.2. Secondary goals:

- To compare the effectiveness of the hybrid cardiac rehabilitation programs with the standard program in terms of:
  - o cardiovascular risk factor control (dyslipidemia, hyperglycemia, hypertension, obesity)
  - o exercise capacity
  - o adherence to physical activity recommendations
  - o adherence to diet recommendations
  - o health-related quality of life
  - o exercise-related adverse events

59

60

### 4. Methodology.

#### 4.1 Design.

A non-inferiority, pragmatic, multicenter, 2 parallel arm, single-blinded, randomized clinical trial will be conducted.

In this non-inferiority study, the objective is to demonstrate that a hybrid exercise-based cardiac rehabilitation model is not inferior (i.e., equivalent or possibly superior) than a standard model. This trial will be pragmatic because it examines the outcomes of the experimental intervention compared with a standard intervention under circumstances which closely approximate the real world. Patients will be recruited in 6 health centers. Personnel undertaking outcome assessment will be blinded to group allocation. Assessment points are shown in the Figure. Finally, randomization process will allow to balance in both groups all, known and unknown, demographic and clinical characteristics that could confuse the association between intervention and results. The trial protocol will be registered ([www.clinicaltrial.gov](http://www.clinicaltrial.gov)), and reported in accordance with CONSORT (29) including the extensions for non-pharmacologic treatment interventions, non-inferiority and equivalence, and pragmatic trials.

#### 4.2. Study population.

The reference population is coronary disease patients. The accessible population is patients that attend one the 6 health centers involved in the study: Complejo Hospitalario San José, Hospital San Juan de Dios, Hospital Padre Hurtado, Hospital Clínico de la Universidad de Chile, Hospital Clínico San Borja Arriarán y Hospital [name] Aravena. The sample will consist of patients in the above centers that meet the following eligibility criteria:

61

62

63

[figure not shown]

64

#### Inclusion criteria:

- Subjects 18 year old or over.
- Patients with coronary artery disease, including Acute Coronary Syndrome (Unstable Angina, Myocardial infarction with or without ST elevation) or stable coronary vessel disease diagnosed by coronariography or a stress test.
- Patients treated medically (i.e., medication only) or by thrombolysis, angioplasty, or revascularization surgery.
- Patients able to attend the health center almost twice a week over three months.
- Patients who owns a mobile phone.
- Patients that consent to participate in the study through signing an informed consent form.

#### Exclusion criteria:

- Patient has a planned repeat cardiac or other procedure in next 12 months.
- Explicit contraindication to perform exercise based on American College of Sport Medicine (30).
- Patients with comorbidities such as dementia, blindness, deafness, serious mental illness, and frailty.
- Musculoskeletal disease that precludes the patient from performing exercise.

#### 4.3. Sample size.

If there is a true difference in favour of the hybrid exercise-based cardiac rehabilitation of 7% in hospitalization rate, then 254 patients are required (127 per group) to be 80% sure that the upper limit of a one-sided 97.5% confidence interval will exclude a difference in favour of the standard exercise-based cardiac rehabilitation group of more than 6%. Considering anticipated loss of follow-up (10%) and the inclusion of an interim analysis that penalizes the power (interim analysis adjustment using Pocock boundary), 314 patients will be recruited (157 per group).

[figure not shown]

This sample size considered the hospitalization and cardiovascular mortality outcomes that was reported in the systematic review by Anderson in 2016 (14), which totaled 18% in the first year of follow-up in those randomized to exercise-based cardiac rehabilitation. The non-inferiority margin was established as is suggested by the Food and Drugs Administration (FDA) (31), which is 50% of the difference between the standard or current therapy (i.e., standard cardiac rehabilitation) and the placebo (or usual care) obtained from a meta-analysis, in this case the same by Anderson (12%).

65

66

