### Secondary goals:

- To compare the effectiveness of the abbreviated cardiac rehabilitation programs with the standard program in terms of:
  - o cardiovascular risk factor control (dyslipidemia, hyperglycemia, hypertension, obesity)
  - o exercise capacity
  - o adherence to physical activity recommendations
  - o adherence to diet recommendations
  - o health-related quality of life
  - o exercise related adverse events

**Methodology:** A non-inferiority, pragmatic, multicenter, parallel, single blinded, randomized clinical trial will be conducted. 314 patients with coronary artery disease including Acute Coronary Syndrome (Unstable Angina, Myocardial infarction with or without ST elevation) or stable coronary vessel disease diagnosed by coronariography or stress test, who have received medical treatment, thrombolysis, angioplasty or revascularization surgery will be recruited consecutively, with written informed consent. Participants will be assigned to experimental or standard rehabilitation programs using a permuted blocked randomization scheme. Concealment of assignment will be preserved. The experimental cardiac rehabilitation program includes medical evaluations, 10 face-to-face exercise sessions, diet and smoking counseling, and distance monitoring with text messages and phone calls, delivered by a physiotherapist. The standard cardiac rehabilitation consists of medical evaluation, 20-24 face-to-face exercise sessions, as well as education sessions about diet and smoking, delivered by a nurse, nutritionist and physiotherapist. The main outcome is a composite of cardiovascular mortality and hospitalizations due to cardiovascular causes (non-fatal stroke, non-fatal myocardial infarction, heart failure, and need of revascularization surgery). Secondary outcomes are cardiovascular risk factor control, exercise capacity, adherence to physical activity and diet recommendations, health-related quality of life and exercise-related adverse events. The outcomes will be measured at the end of intervention, at 6 months, and at 12 month follow-up from recruitment. Only main outcome will be a maximum of three year of follow-up. The sample size was calculated considering 5% of non-inferiority limit. Per protocol and intention to treat analysis will be considered. A survival analysis will be run for the primary outcome. One interim analysis is planned when 50% of patients have completed the evaluation at the end of the first year of follow-up.

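### Section 4.3 and the abstract do not describe one sample size calculation: the margin is 6% in one and 5% in the other, and 254 does not follow exactly from the stated 18% rate

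*Protocol*

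**What the plan says.** Protocol section 4.3 starts from this premise: "If there is a true difference in favour of the hybrid exercise-based cardiac rehabilitation of 7% in hospitalization rate". Its result is "then 254 patients are required (127 per group) to be 80% sure that the upper limit of a one-sided 97.5% confidence interval" will rule out a disadvantage of more than 6 points. Allowance for 10% loss to follow-up and for one interim analysis with a Pocock boundary then raises 254 to 314 (157 per group).

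For the event rate, 4.3 points to hospitalization and cardiovascular mortality in a cited systematic review, "which totaled 18% in the first year of follow-up in those randomized to exercise-based cardiac rehabilitation". It derives the margin as 50% of a 12% difference between standard rehabilitation and usual care, which is 6 points.

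The Methodology paragraph of the Proposal Abstract gives a different margin: "The sample size was calculated considering 5% of non-inferiority limit".

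**The concern.** A sample size statement should let a reader recompute the number from its inputs. Here there are two obstacles.

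- The inputs in 4.3, taken at face value, give a number about 9% below 254 with the usual formula.
- The abstract attributes the same sample size to a margin that 4.3 does not use.

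The margin matters more. It is the threshold by which non-inferiority will be declared, and the section 4.7 analysis plan does not restate it. Two values in one protocol leave room for dispute if the upper confidence limit falls between 5 and 6 points. They also decide whether 254 evaluable patients are more than enough or too few for 80% power.

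**Working it through.** **Inputs from section 4.3:** one-sided 97.5% confidence (z = 1.960), 80% power (z = 0.842), a true difference of 7 points favouring hybrid, a 6-point margin, and 18% under standard rehabilitation. I take 18% as the standard-arm rate, so hybrid is 18 − 7 = 11%. The alternative margin of 5 points comes from the abstract.

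**Plain (unpooled) formula per group:**

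n = (1.960 + 0.842)² × [ps(1 − ps) + pe(1 − pe)] / (ps − pe + margin)²

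Here ps is the standard-arm rate and pe the hybrid rate. The squared z-sum, before rounding the z values, is 7.849.

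**Trying to reproduce 127 per group, 6-point margin:**

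- 18% v 11%: 7.849 × (0.1476 + 0.0979) / 0.13² = 114.02, so 115 per group (230).
- 20% v 13%: 7.849 × (0.1600 + 0.1131) / 0.13² = 126.84, so 127 per group (254), an exact match.
- 18% v 11% with continuity correction, n/4 × [1 + √(1 + 4/(n × 0.13))]² at n = 114.02: 128.94, so 129 per group (258), 1.6% above 254. This formula returns exactly 127 at a standard-arm rate of about 17.7%.
- 18% v 11%, score test with constrained variance: 118.90, so 119 per group (238).

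**At the abstract's 5-point margin:**

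- 18% v 11%, plain: 7.849 × 0.2455 / 0.12² = 133.81, so 134 per group (268).
- 18% v 11%, continuity corrected: 150.02, so 151 per group (302).
- 20% v 13%, plain: 148.86, so 149 per group (298).

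**Power with 127 per group:** Φ[(ps − pe + margin)/SE − 1.960]. The SE is √(0.2455/127) = 0.04397 at 18% v 11%, and √(0.2731/127) = 0.04637 at 20% v 13%. The continuity-corrected version subtracts 1/127 from the numerator.

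| Rates | Margin | Power |
|---|---|---|
| 18% v 11% | 6 points | 84.1% (79.3% with continuity correction) |
| 20% v 13% | 6 points | 80.1% |
| 18% v 11% | 5 points | 77.9% |
| 20% v 13% | 5 points | 73.5% |

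**From 254 to 314:** the protocol gives no interim inflation factor. With an assumed Pocock factor of 1.11 for two looks, 254 / 0.90 × 1.11 = 313.3, so 314. This fits 254 being the number before loss to follow-up, as 4.3 presents it.

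**The case against.** The best defence is that 4.3 names no formula or software, and that 18% v 11% with a standard continuity correction comes within 1.6% of 254. On that basis 127 per group has 79.3% power, in effect the stated 80%. A figure beside the calculation is not shown, and it may contain the missing inputs. The text also never sets out 18% and 11% as a pair: the 7% refers to the hospitalization rate, and the 18% to hospitalization plus cardiovascular mortality. All of this stands.

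It rules out two stronger readings. A reader might infer that 254 cannot come from an 18% rate, or that the design rests on an undisclosed 20% rate because 20% v 13% fits exactly. The documents support neither. With the formula unstated and the rate left free, some rate will always fit, and no 20% rate appears in the text.

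A second defence is that 114 / 0.90 = 126.7, so 127 might already include the 10% loss. This fails, because 4.3 adds the loss after 254. If 254 already contained it, 254 × 1.11 would be about 282, and reaching 314 would count the loss twice.

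A third defence is that any mismatch at 6 points is harmless, since the plain formula asks for fewer patients than planned. That is correct for the 6-point margin. It does not answer the 5% in the abstract: neither formula at 5 points gives 254, and both ask for more.

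**Conclusion.** The point holds in two parts.

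- **Margin.** The abstract and 4.3 contradict each other on the margin behind the sample size. At 5 points and 18% v 11%, 254 patients give about 78% power and the requirement is 268.
- **Derivation.** At 6 points, 254 does not follow exactly from 18% v 11% under any formula tried: 230 plain, 238 by score test, 258 with continuity correction. The plain formula puts the power of 127 per group at about 84%.

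A reader might go on to conclude that the trial is undersized. At the 6% margin derived in 4.3 that is not supported: power is about 79% to 84% at 18% v 11%, depending on the formula, and about 80% at 20% v 13%.

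These results assume that 18% is the standard-arm rate, that the 7-point difference applies to the same composite outcome, that both margins are absolute percentage points, and that 127 per group are evaluable. They do not allow for the interim look, which 4.3 handles through the increase to 314.

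**What to change.** 1. Use one margin throughout. Either correct the abstract to the 6% derived in 4.3, or keep 5%, justify it, and restate N or power to match.
2. In 4.3, give the event rate assumed in each arm and the formula that produced 254, including any continuity correction. If these cannot be recovered, state instead the power that 127 per group delivers at 18% v 11% (about 84% without continuity correction). The sponsor should not adopt 20% v 13% merely because it fits; it should be stated only if it was the rate used, and with its source.

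At the 6% margin this costs wording only and recruitment stays at 314. Keeping 5% with 80% power at 18% v 11% would need 134 / 0.90 × 1.11 = 165.3, so 166 per group (332 in total) by the plain formula and the assumed factor of 1.11. The alternative is to accept and state about 78% power.

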#### 4.4. Recruitment and randomization

The patients will be invited to participate in this clinical trial in the discharge moment, during the first outpatient visit since discharge or emergency attention, or when a coronariography or a stress test has been performed. All information about the study will be delivered by a nurse or physiotherapist in charge on this task exclusively. When the patients consent to participate in the study an initial evaluation will be performed in order to collect baseline sociodemographic and clinical characteristics. The assigning to the experimental or control group will be by permuted blocked randomization. Concealment of assignment will be preserved by an opaque closed envelope.

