#### 4.8. Quality control

All processes involved in the study will be overseen. Specific actions are the following:

- Central management office: a central coordination center will be established, responsible for all general processes in the study such as securing and managing ethical and regulatory approvals, document and questionnaire preparation, field personnel training, measurement standardization, and data entry monitoring. The central coordinator will be responsible maintain regular communication with participating centers, solve problems and supervise the overall integrity of the study.
- Center coordinators: each center will have a local coordinator in charge of trial activities such as recruitment, random assignment, coordination of assessments, and sending data to the central office. The critical issues for which the coordinator is responsible include ensuring assignment concealment and blinding of outcome assessments.
- Monitoring: a professional with documented training in Good Clinical Practice (GCP) (47) will be engaged in order to monitor the conduct of the trial. The purpose will be to verify:
  - The protections of the rights and well-being of participants.
  - That the data obtained will be accurate, complete and checked against source documents.
  - That the study is consistent with the approved protocol, and is undertaken in accordance to the GCP guidelines and ethical requirements.

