## 8.0 Available Resources

**8.1 For field work:** We have a scientific team in epidemiologic and clinical studies, that at present is participating in the PURE cohort (3585 participants) and CESCAS cohort (1950 participants). There is also available trained professionals who will deliver the study interventions (physiotherapists), and others who will perform the outcomes measurements in the centers identified (i.e., in each center one coordinator who will be in charge of all processes involved has been identified). The centers have given an anticipate support for conducting the study (upon approval of all regulatory requirements), have capability to implement the interventions, and have cardiac rehabilitation demand that justifies the feasibility of recruitment of the required sample size for the study (around 500 patients per year, and more than 800 in the timeline estimated for recruitment).

The centers are: Complejo Hospitalario San José, Hospital San Juan de Dios, Hospital Regional de Antofagasta, Hospital Clínico de la Universidad de Chile, and Hospital Clínico San Borja Arriarán in Santiago, and Hospital [name] Aravena in Temuco.

**8.2 Research team configuration:** blend seniors with young researchers, and methodological and clinician expertise. We have experience in management of big scale studies, in statistical analyses, database construction, and data entry supervision.

97

98

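### One local coordinator per centre is responsible for recruitment, for assignment by envelope in permuted blocks and for concealment itself, so allocations could be anticipated if blocks are kept per centre

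*Protocol*

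**What the plan says.** On method, protocol section 4.4 says: "The assigning to the experimental or control group will be by permuted blocked randomization". On concealment, it says: "Concealment of assignment will be preserved by an opaque closed envelope".

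On roles, section 4.8 says that "each center will have a local coordinator in charge of trial activities such as recruitment, random assignment, coordination of assessments". It continues: "The critical issues for which the coordinator is responsible include ensuring assignment concealment and blinding of outcome assessments". Section 8.1 (under Available Resources) confirms that this is one person: "in each center one coordinator who will be in charge of all processes involved has been identified".

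Two other parts of the text bear on the point. Section 4.4 brings in a further person at the invitation stage: "All information about the study will be delivered by a nurse or physiotherapist in charge on this task exclusively". It then describes consent and a baseline evaluation before it describes assignment. Section 4.8 also plans a central office: "a central coordination center will be established, responsible for all general processes in the study". Random assignment, however, is listed among the tasks of the centre coordinators.

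On masking, section 4.1 calls the trial single-blinded, with outcome personnel blinded, and section 4.6 adds a blinded adjudication committee. Patients and therapists cannot be blinded, because the arms differ visibly: 10 face-to-face sessions plus texts and calls, against 20-24 face-to-face sessions (proposal abstract).

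**The concern.** Concealment means that nobody who influences whether or when a patient is enrolled can know, or make a good guess at, the next assignment. Here the person charged with protecting concealment is also responsible for recruitment and for assignment. That person has the envelopes in hand and can know which arm earlier patients at the centre received. Permuted blocks make the recent history informative about what comes next.

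If allocations were anticipated, an approach to a patient could be brought forward, delayed or not made, depending on the expected arm. The arms would then differ in underlying risk before treatment starts. In this trial one direction matters most. If patients thought to be at lower risk tended to enter when the hybrid arm was expected, the difference would shift towards a false conclusion of non-inferiority.

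The later safeguards in the plan do not reach this problem. Blinded adjudication (section 4.6) protects how events are classified, not whether the groups are comparable. The ITT and per-protocol analyses (section 4.7, item 6a) both compare groups formed by the same assignments, so both would carry the same selection. Adjustment (item 6b) is planned only for baseline imbalances that are found, and it cannot act on risk that was not measured.

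**Working it through.** The protocol gives no figure to reproduce on this point. It does not state the block size, whether sizes vary, or whether the list is kept per centre. The calculation below therefore shows a range under stated assumptions.

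**Inputs from the protocol.** Permuted blocks and envelopes (4.4); 314 patients, 157 per group (4.3); 6 centres (4.1), so 314/6 = about 52 per centre if recruitment is even (assumption); non-inferiority margin of 6 points (4.3; the abstract gives 5%).

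**Step 1: blocks kept per centre, size fixed and known, past allocations known (all assumed).** At each position the best guess is the arm with more places left in the block; a tie counts as one half.
- Block of 4, chance of a correct guess at positions 1 to 4: 1/2, 2/3, 2/3, 1. Mean = 2.833/4 = 70.8%.
- Block of 6, positions 1 to 6: 0.5, 0.6, 0.6, 0.7, 0.7, 1. Mean = 4.1/6 = 68.3%.
- Share of allocations known with certainty is 1/(m + 1) for a block of size 2m: 1/3 = 33% for size 4, 1/4 = 25% for size 6.

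**Step 2: per-centre blocks of randomly varied, unknown size (assumed).** Simulating 52 patients at one centre and guessing the arm that is behind gives 69.0% correct with sizes 4 and 6, and 67.7% with sizes 4, 6 and 8. Varying the size makes certainty harder to reach but hardly reduces guessing.

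**Step 3: one list across all six centres, each coordinator seeing only the local allocations (assumed).** Simulating 314 patients spread at random over 6 centres gives about 51% correct for blocks of 4, 6 or 8, which is close to chance.

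**Step 4: what this could mean for the risk difference.** Suppose a share s of entries can be steered, the patients steered to the two arms differ by d in 12-month risk, all steering goes the same way, and the guess is right with probability p. Then bias = s x d x (2p - 1). The protocol gives neither s nor d. Taking s = 10-30% and d = 10-20 points purely for scale:
- Per-centre blocks of 4 (p = 0.708, 2p - 1 = 0.417): 0.10 x 10 x 0.417 = 0.4 points, up to 0.30 x 20 x 0.417 = 2.5 points.
- One shared list (p = 0.51, 2p - 1 = 0.02): 0.10 x 10 x 0.02 = 0.02 points, up to 0.30 x 20 x 0.02 = 0.12 points.

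The answer turns mainly on how the list is organised, and the protocol does not say. Envelopes opened under a local coordinator make per-centre sets the more natural reading, but that is an inference.

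**The case against.** The strongest reply is that the protocol names a recognised method, opaque envelopes with permuted blocks, contradicts itself nowhere on this, and leaves operational detail to other documents. Block size is often kept out of a protocol on purpose. Much of that stands. The unstated block size and the unstated stratification by centre are missing detail, not errors, and no complaint is made of either.

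A reader might also infer more than the text supports:
- That the coordinator personally recruits. The text says in charge of recruitment, and section 4.4 gives the informing of patients to a dedicated nurse or physiotherapist. It does not say whether that person is independent of the coordinator or unaware of earlier allocations.
- That allocations can be predicted outright. This needs lists kept per centre and knowledge of past allocations, and certainty also needs a known or guessed block size. None of these is stated.
- That the central office is excluded from allocation. Its tasks are given as examples, so the text is silent on this.
- That assessment is compromised. The coordinator coordinates assessments, while assessors and adjudicators are said to be blinded.

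The described order (consent and baseline, then assignment) and the GCP-trained monitor in 4.8 are real safeguards. The order does not, however, stop someone from choosing when or whether to approach a patient.

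What the reply does not answer is the concentration of roles. The protocol fixes that itself, and its assurance that concealment will be kept does not address it.

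**Conclusion.** The point holds as a weakness of the stated method: responsibility for recruitment, assignment by envelope in blocks, and concealment rests with one person per centre, in a trial open to patients and therapists. Upcoming allocations could be anticipated if blocks are kept per centre. For a known block size of 4 or 6, about 68-71% could then be guessed; with one list across the six centres, about 51%.

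The documents do not support a statement that enrolment will be steered, nor any particular bias. The figures in points are conversions of assumed inputs and run from almost nothing to less than half of the 6-point margin. The reason to act is that a failure of concealment cannot be fully repaired after enrolment, while a better method is at hand at small cost. This is a worthwhile, cheap improvement and not a fatal flaw.

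**What to change.** Amend sections 4.4 and 4.8 as follows:
- The planned central coordination centre holds the sequence and releases each assignment by telephone or web, only after consent, eligibility and baseline data are recorded.
- Block sizes are not disclosed to sites.
- The person who enrols has no access to the sequence, and assignment is separated from responsibility for recruitment.

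Central release takes the envelopes out of the centre and ties each assignment to a patient already registered. It does not by itself stop guessing from past allocations if blocks are kept per centre (step 2 of the working), so the separation of roles matters as much as the undisclosed block size.

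The cost is a short amendment and an allocation log or web form at an office already planned. The downside is that sites must contact the centre before each assignment.
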